#### Follow-Up at 4 Months and 8 Months

Primary outcome measures (sleep diary and actigraphy), secondary outcome measures (questionnaires), and measures to address exploratory questions are administered to all participants at baseline and at 4 and 8 months postrandomization. Participants receive an automated invitation email from REDCap to start their 4-month follow-up after 16 weeks postrandomization, and to start their 8-month follow-up 32 weeks postrandomization.

If participants do not begin follow-up assessment, research staff members make 12 attempts to contact participants by email and telephone at different times of day (eg, afternoon, evening) and various days of the week (eg, weekday, weekend), over the course 6 weeks (from 14 weeks postrandomization to 20 weeks postrandomization at 4-month follow-up, and 30 weeks to 36 weeks postrandomization at 8-month follow-up). This procedure is designed to maintain communication with participants and ensure that outcome data are collected. Participants are deemed lost to follow-up for that assessment period if 4-month and 8-month assessments are incomplete by 20 weeks or 36 weeks postrandomization, respectively.

#### Compensation

To compensate participants for their time and to maximize adherence rates, participants receive an honorarium of $25 CAD for the completion of all measures at each of the 3 collection time points, as well as a completion stipend of $25 CAD at the end of the 8-month follow-up, if they completed all 3 assessments. Therefore, a maximum of $100 CAD per participant is given as an honorarium for study participation. At study completion, participants are entered into a draw to win a tablet; one entry is generated for each day that the participant completed the sleep diary and has corresponding actigraphy data.

### Statistical Analysis

#### Sample Size Analysis

A total goal of 500 consented participants is expected. Using the assumption that 50.0% (250/500) of participants will be lost to follow-up, the target sample size at the end of the study is n=250 [107-109]. This gives us power of .80 to detect a significant group-by-time interaction with the effect size (*d*)=0.45 and alpha set to .025, for primary outcome measures calculated from actigraphy and sleep diary from baseline to 4-month follow-up. Given that 2 primary outcome variables are being used (sleep efficiency from actigraphy and sleep efficiency from sleep diaries), alpha was divided by 2 so that *P*=.025, rather than *P*=.05 would be accepted as indication of statistical significance. This is based on the assumption that an effect size of *d*=0.45 is clinically significant for sleep efficiency as measured by actigraphy and sleep diary [45].

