### Rationale

The Better Nights, Better Days (BNBD) program, which is an eHealth intervention for primary caregivers of children ages 1 to 10 years who present with insomnia, can bridge this knowledge to practice gap by providing a potential solution to one of the most common treatment barriers—access to care. BNBD is an innovative, bilingual (English and French) eHealth program for parents, which aims to provide accessible and evidence-informed care for insomnia in typically developing children.

This paper presents the protocol for a planned RCT to evaluate the effectiveness of the BNBD intervention for the treatment of insomnia in children. This is a 2-arm design, using an equal allocation ratio of 1:1, comparing participants assigned to the intervention group who receive the BNBD intervention (treatment) and those assigned to the usual care group who do not receive the BNBD intervention and are able to access other treatment resources (control). Assessments are conducted at 3 periods: baseline (pretreatment), 4 months postrandomization (end of treatment), and 8 months postrandomization (follow-up). To assess the impact of the intervention, the primary outcome measure of sleep efficiency is evaluated using data collected from actigraphs worn by children and sleep diaries completed by parents. Sleep efficiency is the ratio of total time spent asleep to the total amount of time spent in bed. In addition, secondary outcomes are captured by questionnaires that are collected to evaluate children’s sleep and psychosocial health, as well as parental daytime functioning and psychosocial health outcomes.

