#### Primary Objective and Hypothesis

The primary objective is to assess the *immediate impact* (baseline vs 4 months) of the intervention on children’s sleep.

We hypothesize that at the end of the 4-month assessment period, children randomized to the intervention group will evidence improvement in their symptoms of insomnia compared with children in the usual care group. The outcome variables are sleep efficiency collected by both an objective measure (actigraphy) and a parent report measure (sleep diary).

There are 2 hypotheses for the primary outcome:

We hypothesize that children in the intervention group will show improvements in sleep efficiency calculated using *actigraphy* data compared with the usual care group.We hypothesize that children in the intervention group will show improvements in sleep efficiency calculated using *sleep diary* data compared with the usual care group.

Note that sleep efficiency is a measure that captures both sleep quantity and quality and is defined as the amount of total sleep time divided by the amount of time spent in bed with the goal to be sleeping. For example, if a child went to bed at 8 PM and woke at 8 AM, but took 1 hour to fall asleep and was awake for 30 min throughout the night, the child’s sleep efficiency would be 87.5% (ie, (630 min/720 min) × 100).

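### The fixed .025 threshold for each of the two primary outcomes is valid, but Holm's step-down test holds the same .05 family-wise error with more power, at small cost

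*Protocol article*

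**What the plan says.** Under Primary Objective and Hypothesis, the protocol article states "There are 2 hypotheses for the primary outcome", one for actigraphy and one for the sleep diary. It does not say whether one or both must succeed.

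Under Sample Size Analysis it gives "power of .80 to detect a significant group-by-time interaction" with "the effect size (*d*)=0.45 and alpha set to .025". It sets the decision rule in the same place: "alpha was divided by 2 so that *P*=.025, rather than *P*=.05 would be accepted as indication of statistical significance". This is a significance criterion as well as a planning value. The analysed number is given by "the target sample size at the end of the study is n=250", after assuming that "50.0% (250/500) of participants will be lost to follow-up". Allocation is described under Rationale as "using an equal allocation ratio of 1:1", so 125 per arm are analysed.

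No step-down, gatekeeping or alpha-recycling rule appears anywhere in the article.

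**The concern.** Each outcome is held to .025 whatever the other shows. Once one outcome has been declared significant at .025, only one hypothesis of the pair remains in doubt, and it can be tested at .05 without the family-wise error exceeding .05. The fixed split does not use this. The loss falls where one outcome is clearly positive and the other is borderline: a second P value of .03 or .045 is declared negative.

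That case matters here. Under Data Analysis the article explains that actigraphy is included because unblinded trials tend to favour the active treatment, and that the parents' view is also needed. The investigators therefore have an interest in a conclusion on both measures, and joint success is where a step-down rule gains most.

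**Working it through.** **Inputs from the protocol article.** Two primary outcomes; alpha .025 each; power .80 per outcome; d = 0.45; 250 analysed (125 per arm); 50% loss.

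**Assumptions.** Two-sided tests, because sidedness is not stated. The correlation between the two test statistics is not given, so 0, .3 and .5 are shown.

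**Step 1: the plan's own figures.**
- Alpha: .05/2 = .025. If the tests are independent, the family error is 1 − (1 − .025)² = .0494, and it is at most .05 under any dependence. The rule is valid.
- Sample size: 250/(1 − .5) = 500, as stated.
- Power: a simple two-group comparison at 125 per arm has noncentrality 0.45 × √(125/2) = 3.558. With critical value 2.241 this gives power Φ(3.558 − 2.241) = .906, not .80. A change-score test with a baseline-to-follow-up correlation of about .335 does give .80 at 250. The comparison below is therefore calibrated to the stated .80, with .906 as a sensitivity case.

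**Step 2: the two rules.**
- Bonferroni: reject each outcome if its P ≤ .025.
- Holm: test the smaller P at .025; if it is significant, test the larger at .05.

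**Step 3: closed form for independent tests at .80.** The noncentrality is 2.241 + 0.842 = 3.083. Power at .05 is Φ(3.083 − 1.960) = .869.
- Per outcome under Holm: .80 + .80 × (.869 − .80) = .855.
- Both under Bonferroni: .80² = .640. Both under Holm: .640 + 2 × .80 × .069 = .750 (.751 unrounded).

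**Step 4: simulation with correlated tests** (4 million draws, power .80 per outcome under Bonferroni).

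| Correlation | Per outcome, Bonferroni → Holm | Both, Bonferroni → Holm | At least one, either rule |
|---|---|---|---|
| 0 | .80 → .856 | .640 → .751 | .960 |
| .3 | .80 → .850 | .666 → .765 | .934 |
| .5 | .80 → .845 | .687 → .778 | .913 |

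With power .906 per outcome, the chance of winning on both goes from .821 to .892 at correlation 0, and from .842 to .900 at correlation .5.

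**Step 5: error rates.**
- With no true effect on either outcome, the family error is the same under both rules: .049, .049 and .047 at correlation 0, .3 and .5.
- With a real diary effect (power .80) and no actigraphy effect, actigraphy is falsely declared positive .025 of the time under Bonferroni, and .045, .044 and .042 under Holm.

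**Step 6: a weaker objective effect (assumed, not in the article).** Take d = 0.30 for actigraphy, d = 0.45 for diary and 125 per arm on the simple two-group test. The actigraphy noncentrality is 0.30 × √62.5 = 2.372, and power rises from .55 to .65. If the scale is calibrated to the stated .80 instead, it rises from .43 to .52.

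**The case against.** The strongest reply is that nothing here is wrong. The rule is pre-specified, the test level agrees with the planning level, and the family error is controlled. That stands: this is a point of efficiency. A reader might infer that the split is a statistical error, and the document does not support that.

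A reader might also infer that Holm is free, which is not so.
- The false-positive rate for actigraphy taken alone goes from .025 to about .044 when only the diary effect is real. This remains within .05, but it is a cost on the objective outcome.
- The diary is parent-reported and participants know their group. If reporting bias produced a diary win, that win would relax the actigraphy threshold. Holm's guarantee presumes a valid diary P value. The article does not give this as its reason for the fixed split, but it is a defensible one.
- Bonferroni has simple matching 97.5% intervals and Holm does not. An actigraphy P of .03 could be significant under Holm while its 97.5% interval includes zero.

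The gain also depends on what counts as success. The chance of winning on at least one outcome is unchanged, and the article does not require both. The benefit lies in the second outcome and in joint success.

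Finally, the gap between .80 and .906 in the working might be read as a power error. An unstated baseline-to-follow-up correlation can explain it, so it is not shown to be one, and the comparison of the two rules does not rest on it.

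**Conclusion.** The point holds as an improvement to a valid rule. Holm rejects everything the fixed split rejects, holds the family-wise error at .05 whatever the dependence between outcomes, and needs no more participants. At the stated power of .80 the gain is about 5 points per outcome and about 9 to 11 points for winning on both, with none for winning on at least one. These sizes rest on two-sided tests and an assumed correlation of 0 to .5. The ordering of the two rules rests on neither. The gain of about 10 points for actigraphy in the weaker-effect case depends on an assumed d of 0.30 and is only an illustration. To call half the alpha wasted would overstate a gain of 5 points per outcome.

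**What to change.** Before unblinding, replace the fixed threshold with one sentence: the smaller of the two primary P values is tested at .025 and, if it is significant, the other is tested at .05. Keep .025 as the conservative planning alpha, so the sample size does not change. The timing matters, because adopting the rule after a P value of .03 has been seen would not be credible.

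Add a second sentence on intervals. Either label the reported intervals (for example 95%) as not adjusted for multiplicity, or state that they need not agree with the step-down decision. Also state that the error on either outcome alone can rise above .025 but stays within .05. If the investigators prefer to keep the actigraphy threshold independent of the diary result, they can keep the fixed split and give that as the reason. Either way the cost is two or three sentences of text and no extra participants.

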#### Data Analysis

The primary outcome variables that will be used to evaluate the impact of the intervention program on insomnia symptoms are sleep efficiency from actigraphy and sleep efficiency from sleep diary data. Overall, 2 primary outcome measures are included to capture these variables of interest using both an objective measure of sleep (ie, actigraphy) and a parent report/subjective measure of sleep (ie, sleep diary), thus allowing us to compare our results with existing research in the field. In unblinded RCTs (ie, in which participants know their group assignment such as this study), there is evidence of bias toward significance of the active treatment; thus, an objective measure (eg, actigraphy) is used to mitigate this bias [110]. However, as parents are the primary decision makers with respect to seeking treatment for their child’s health problems, it is also critical to obtain their perspective. Further, inclusion of patient-reported outcomes is recommended when testing interventions [111].

Secondary outcomes for this study examine the maintenance of changes in sleep, as well as the impact on the child’s psychosocial health (behavioral, attentional, and emotional functioning) and on parents’ psychosocial health (ie, psychological adjustment). Data analyses are overseen by the research team, including the statistician, using an intent-to-treat data analytic approach [112].

Conditional growth model methodology, also known as hierarchical models, a generalization of the standard linear model, which permits data to exhibit correlation and nonconstant variability, will be used to fit each outcome at baseline, 4 months, and 8 months [113] using PROC MIXED in the Statistical Analysis System. Model formulation is at 2 levels, with participants as level 1, and treatment group as level 2. The level 1 model is a linear individual growth model, and the level 2 model expresses variation in parameters from the growth model as random effects unrelated to any person-level covariates. For each parent, the actual time (in days) from baseline to when each follow-up assessment is completed is also entered, to account for variation in when parents actually complete assessments.

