##### Primary Outcome

For the primary outcome (sleep efficiency based on actigraphy and sleep diary data), we will test for a significant interaction effect between time and group, which would indicate differential rate of change over time between groups. Differences in the estimated means between the intervention group and usual care group will also be compared at the 4-month post treatment time point (primary end point) to determine the magnitude of differences between groups [114].

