##### Secondary Outcome

For the secondary outcomes, we will test differences between the 2 groups modeling changes in the outcome variables across the 3 points of measurement (baseline, 4 months, and 8 months postrandomization) to determine treatment effects at 8 months postrandomization. Again, a significant time × group interaction would indicate differential rate of change over time between groups. Differences in the estimated means at the 4-month and 8-month posttreatment time points will also be examined.

To examine the possibility of differential response to treatment across the 3 age groups, we will use a growth curve modeling of the 2 primary outcomes (sleep diary and actigraphy). Analysis is based on the methodology of the extension of the generalized linear model for longitudinal data, namely marginal and random effects modeling, which allows for varying intercepts and slopes across subjects, “G-side” random effects, and different within-person error variance covariance structure, “R-side” random effects [115,116]. An interaction of age group (toddler, preschool-aged, and school-aged) × time (3 assessments) × randomization group (intervention and usual care) would indicate differential response to treatment.

An intent-to-treat analysis will be conducted. Multiple imputation techniques will be used to deal with missing data. This method works well on longitudinal data and is robust to violations of non-normality of the variables used in the analysis.

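### The two-level description of the primary model contradicts the time-by-group test it is meant to support: levels are mislabelled and, read literally, there is no treatment term

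*Protocol article*

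**What the plan says.** All references are to the protocol article, Statistical Analysis part of the Methods.

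- **Data Analysis, name of the method:** "Conditional growth model methodology, also known as hierarchical models, a generalization of the standard linear model". It is to be fitted to each outcome at baseline, 4 months and 8 months, with actual days from baseline entered as time.
- **Data Analysis, levels:** "Model formulation is at 2 levels, with participants as level 1, and treatment group as level 2".
- **Data Analysis, level 1:** "The level 1 model is a linear individual growth model".
- **Data Analysis, level 2:** "the level 2 model expresses variation in parameters from the growth model as random effects unrelated to any person-level covariates".
- **Primary Outcome:** "we will test for a significant interaction effect between time and group, which would indicate differential rate of change over time between groups". A comparison of estimated means at 4 months is added.
- **Secondary Outcome, age-group analysis of the same two outcomes:** the method is one "which allows for varying intercepts and slopes across subjects".

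Two other sections bear on this. Sample Size Analysis powers the trial for the group-by-time interaction. Randomization allocates individual parents 1:1 in blocks of 4 within three age groups.

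**The concern.** The sentences in Data Analysis do not describe one model. An individual growth curve is fitted to repeated occasions within a person, so its level-1 units are assessments and its level-2 units are persons. The stated labels move both up one step, to participants and arms.

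The sentence on level 2 makes this worse. Arm is a property of the participant, so a level 2 unrelated to any person-level covariate has no place for it. A model of that kind is normally called unconditional, whereas the paragraph calls it conditional.

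This is the only model specification the article gives for the two co-primary outcomes. If it contradicts itself, whatever model is fitted will depart from some part of the published text. A reader of the results could not then tell a correction from a post hoc choice.

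**Working it through.** The question is which parameters exist in the model as written, so most of the check is structural.

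**1. Level 1, as stated.** For child *i* at occasion *j*, a linear individual growth model is

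Y_ij = π0_i + π1_i · t_ij + e_ij.

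The index *j* runs over three assessments within a child. Level 1 is therefore occasions, not participants.

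**2. Level 2, read literally.** Growth parameters vary only as random effects, with no person-level covariate:

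π0_i = γ00 + u0_i and π1_i = γ10 + u1_i.

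Substituting gives Y_ij = γ00 + γ10 · t_ij + u0_i + u1_i · t_ij + e_ij. There are two fixed parameters, an intercept and a time slope. Neither involves arm.

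**3. Level 2, as the primary test requires.** With G_i the arm of child *i*:

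π0_i = γ00 + γ01 · G_i + u0_i and π1_i = γ10 + γ11 · G_i + u1_i.

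Substituting adds γ01 · G_i and γ11 · G_i · t_ij. The test under Primary Outcome is a test of γ11, which step 2 does not contain.

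**4. Demonstration.** One data set was simulated with 250 participants (125 per arm) and 3 occasions each, 750 records in all. The assumed SDs were 0.7 for the intercept, 0.05 per month for the slope and 0.7 for the residual. The true interaction was 0.45/4 = 0.1125 per month. These variances are assumptions, and the fits only show which parameters each model has.

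| Model fitted | Fixed effects | Group-by-time term |
|---|---|---|
| Random intercept and slope per participant, no covariates (step 2) | intercept, time | none |
| Same, plus arm and arm-by-time (step 3) | intercept, time, arm, arm-by-time | 0.129 per month, SE 0.017 |
| Arm as the level-2 unit (labels taken literally) | intercept, time | none; between-arm slope variance rests on 2 units, with a boundary fit and a Hessian that is not positive definite |

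Only the second model supports the stated test.

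**5. Plan figures.** The stated arithmetic on attrition and alpha reproduces: 500 × 0.5 = 250 and .05/2 = .025. The stated power of .80 does not reproduce directly. Taking d on the scale of the analysed variable, with 125 per arm, d = 0.45 and two-sided alpha .025, power is 0.906. For a change score with d on the single-occasion SD, .80 would need a baseline-to-follow-up correlation of about 0.33, which the article does not state. That is a separate matter. None of these inputs depends on how the levels are labelled.

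**The case against.** **The intended test is clear.** Sample Size Analysis, Primary Outcome and Secondary Outcome all refer to a time-by-group interaction, and the model is called conditional. A competent statistician reading them together would include arm and arm-by-time. This stands, and it limits the point to a misdescribed model.

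**A charitable reading exists.** Naming treatment group at level 2 could be shorthand for the level at which that predictor enters. The exclusion of person-level covariates could mean none beyond arm, or could state the usual independence of random effects and covariates. The first sentence alone allows this. The second does not say it: it excludes any such covariate, makes no exception for arm, and arm is allocated per parent. The reader has to supply the exception.

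**It is a condensed article.** Full equations and covariance structure belong in the analysis plan, which is not shown. That would answer a complaint about missing detail. It does not answer one about sentences that are present and conflict.

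**Stronger readings that the documents do not support.** A reader might infer that the trial would analyse its two arms as a random sample of clusters, leaving one degree of freedom for the treatment comparison. Nothing says this. Individuals are randomized, and a model with arm as a random level-2 unit has no fixed interaction coefficient to refer to one degree of freedom. A reader might also infer that correlation within a child is ignored. The same paragraph says the method accommodates correlated data, and Secondary Outcome names both subject-level random effects and a within-person error structure.

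**Conclusion.** The point holds as a contradiction in how the primary model is specified. The level labels are wrong for an individual growth model. The sentence on level 2, taken at its word, removes the treatment terms that the primary test needs. No other section corrects it.

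The effect is on clarity and prespecification for both co-primary outcomes. No sample size, alpha or power figure changes, and no numerical loss can be attached to it. It would be too strong to say that the trial has no group-by-time test, because that test is stated repeatedly. The conclusion assumes that treatment arm counts as a person-level covariate, which follows from individual randomization. It deserves correction because the text concerns the primary analysis and the repair is nearly free.

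**What to change.** Rewrite the two sentences on levels in Data Analysis so that:

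- level 1 is the assessments (baseline, 4 and 8 months) within a child;
- level 2 is the child, with a random intercept and a random slope;
- treatment arm and arm-by-time enter as fixed effects, and the arm-by-time coefficient is identified as the primary test;
- the age-group stratification factor enters as a fixed covariate, to match the randomization;
- the phrase "random effects unrelated to any person-level covariates" is deleted.

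The linear time term in actual days can stay. Replacing it with categorical visits, or choosing an unstructured residual matrix, would be a different modelling decision and is not needed here. If the analysis plan already states the model this way, a published clarification that refers to it would do.

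The cost is a few sentences of text. Data collection, sample size and alpha are untouched. The change should be dated before the allocation code is released to the statistician running the primary analysis.
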